### Schedule

The participants will be registered from December 1, 2021, to December 31, 2023. The end date of follow-up is December 31, 2024.

## Discussion

The main aim of the present study is to evaluate the efficacy and safety of patients with recDCM who received half-dose neurohumoral blockades and received original dose maintenance therapy, and then by comparing the two doses of treatment, it may be concluded that “ACEI/ARB/ARNI + beta-blockers” halving dose was non-inferior to patients' maintenance dose in maintaining recovered cardiac function in DCM patients. This will provide a significant basis for the choice of whether to reduce dosage or to adhere to original dose maintenance therapy in DCM patients who recovered, to reduce the economic and psychological burden on patients.

Furthermore, this study is only the pilot study of the original research we want to do because the ethics committee needs to protect the interests of patients. Therefore, one of the limitations of this study is the small sample size, and if this study is effective, we will conduct more research.

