**Discussion:**

The study will provide important evidence of whether it is safe and effective to halve the dosage of neurohumoral blockades in recDCM patients.

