### Sample size

Regarding the results from clinical trials in heart failure patients, the incidence of cardiac death or heart failure readmission within 12 months is 15–30% with guideline-directed medical therapy. The patients with DCM enrolled in this study have recovered cardiac function and ejection fraction, and TRED-HF study showed a primary endpoint event rate of 0% in such patients with medication doses unchanged in 6 months. Thus, in this study, it is estimated that the primary endpoint rate in control group and in withdraw group is 5 and 7% over 12 months of follow-up. It is estimated that 218 patients would provide the trial with 80% power to show the non-inferiority of halved doses to original doses, a two-sided alpha of 0.05 and a non-inferiority margin of 10% is applied. Considering a loss to follow up rate of 10%, the final sample size is 240. According to the suggestion of the ethical committee, the current study is a pilot study and 50 patients are intended to be included initially, 25 patients per group. After the initial analysis, more patients might be recruited in a further stage of the study.

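### The Discussion offers non-inferiority as a possible conclusion of a 50-patient pilot, which at the stated alpha can exclude the 10-point margin only if the half-dose arm has fewer events than control

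*Protocol article*

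**What the plan says.** Sample size assumes that the "primary endpoint rate in control group and in withdraw group is 5 and 7" per cent respectively over 12 months. It states that "218 patients would provide the trial with 80% power to show the non-inferiority of halved doses to original doses", with "a two-sided alpha of 0.05 and a non-inferiority margin of 10% is applied". The total is then raised for loss: "Considering a loss to follow up rate of 10%, the final sample size is 240". The same paragraph goes on to say that "the current study is a pilot study and 50 patients are intended to be included initially, 25 patients per group", and that more patients might be added at a later stage.

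The first paragraph of the Discussion, describing the main aim of the present study, says the comparison may support the conclusion that the "halving dose was non-inferior to patients' maintenance dose in maintaining recovered cardiac function in DCM patients". It adds, without a hedge, that this will be an important basis for deciding whether to reduce or keep the dose. The second paragraph says the study is only a pilot and names the small sample as a limitation. It does not withdraw the non-inferiority conclusion, and it does not say that the margin cannot be tested adequately with 50 patients.

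Statistical analysis plans a Cox hazard ratio with a 95% confidence interval. It names no interval for the risk difference.

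**The concern.** The conclusion is attached to a study about a quarter of the size that the protocol calculates for it (50 against 218, before loss). Few events are expected. At the planned rates, 25 per arm gives 25 × 0.05 = 1.25 events on control and 25 × 0.07 = 1.75 on half dose. A result with very few events in both arms is therefore plausible, and the Discussion invites the reader to take it as non-inferiority of a reduced dose.

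At stake is false reassurance. Such data would be compatible with an excess of relapse larger than the 10 points that the protocol itself sets as its limit. The Background reports significantly more recurrence after complete withdrawal in the earlier trial, so the possibility of an excess is not remote.

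**Working it through.** **Inputs**
- Rates 5% (control) and 7% (half dose), margin 10%, two-sided alpha 0.05, power 80%, total 218: Sample size.
- 25 per arm: Sample size. 1:1 allocation: Randomization. 95% interval: Statistical analysis.
- Assumption: the margin is an absolute risk difference. The scale is not stated, but 218 reproduces on it.

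**1. The plan's own figure**

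n per arm = (z_alpha + z_beta)² × [0.05 × 0.95 + 0.07 × 0.93] / (0.10 − 0.02)², where the bracket is 0.1126 and the denominator 0.0064.
- One-sided 0.05: (1.645 + 0.842)² × 0.1126 / 0.0064 = 108.8, so 109 per arm and 218 in total. This matches.
- One-sided 0.025, which is the stated two-sided 0.05: (1.960 + 0.842)² × 0.1126 / 0.0064 = 138.1, so 139 per arm and 278 in total. This does not match.

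The stated alpha and the stated 218 therefore disagree. That is a separate matter, but because of it both levels are carried below.

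**2. Upper limit for the risk difference at 25 per arm, stated alpha (95% interval)**

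The Wilson upper limit for 0/25 is z² / (n + z²) = 3.8415 / 28.8415 = 0.133. The Wilson limits for 1/25 are 0.0071 and 0.1954. Newcombe upper limit = difference + √[(U_half − p_half)² + (p_control − L_control)²].
- 0 vs 0 (half dose vs control): 0 + √(0.1332² + 0²) = 13.3 points
- 1 vs 1: 0 + √(0.1554² + 0.0329²) = 15.9
- 2 vs 2: 17.9
- 0 vs 1: −0.04 + √(0.1332² + 0.0329²) = 9.7
- 1 vs 2: 12.6
- 1 vs 3: 9.4

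Other methods for 0 vs 0 give Miettinen-Nurminen 13.6, exact binomial 1 − 0.025^(1/25) = 13.7 and Agresti-Caffo 10.07. All exceed 10. Across every possible table at 25 per arm, Newcombe never excludes 10 points when the half-dose arm has as many events as control or more. With no events in either arm, about 35 or 36 per arm would be needed.

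**3. Chance of excluding the margin at 25 per arm (sum of binomial probabilities over qualifying tables)**
- Rates 5% / 7%: 15.9%
- Rates 5% / 5%: 24.9%

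**4. The same at one-sided 0.05 (90% interval)**
- 0 vs 0: Newcombe 9.8 and Miettinen-Nurminen 9.9, which just clear. The exact bound is 1 − 0.05^(1/25) = 11.3, which does not (exact p = 0.9^25 = 0.072).
- 1 vs 1: Newcombe 12.5
- Chance at 5% / 7%: 28.3%

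**5. With loss to follow-up**

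The planned 10% loss leaves about 22 per arm. For 0 vs 0, Newcombe gives 14.9 (95% interval) or 11.0 (90% interval). At the 95% level even 0 vs 1 fails, at 10.8. The chance at 5% / 7% falls to about 7% (95% interval) or 17% (90% interval).

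**6. Methods that break down with no events**

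At 0 vs 0 a Wald interval has zero width and would appear to exclude any margin. The planned Cox hazard ratio cannot be estimated.

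**The case against.** The strongest reply is that the protocol already separates the pilot from the powered trial. Sample size ties the power and margin to 218 patients, the title and abstract carry the pilot label, and the Discussion concedes the small sample. The sentence on non-inferiority is conditional and sits in a Discussion; it is not a decision rule, and Statistical analysis sets no non-inferiority test for the pilot. All of this is true, and it lowers the severity. It does not remove the point, because the conclusion and its use for dose choice are attributed to the present study and the caveat leaves both standing.

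Several stronger readings are tempting but not supported:
- **That 50 patients cannot show non-inferiority at all, or that 0 vs 0 always fails.** A result of 0 vs 1 or 1 vs 3 excludes the margin at the stated alpha. At the one-sided level that reproduces 218, 0 vs 0 just clears by score methods.
- **That power falls from a claimed 80% to 16%.** The protocol never claims 80% power for 50 patients, and the two figures use different alpha levels. On one normal approximation, 218 against 50 patients gives 80% against 33% at one-sided 0.05, and 70% against 22% at the stated two-sided 0.05.
- **That the abstract overclaims.** "The study will provide important evidence of whether it is safe and effective to halve the dosage" promises evidence on a question and asserts no result. Rewording it is a matter of taste.
- **That the pilot must adopt recruitment or adherence aims.** That is also a preference and not a correction.

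**Conclusion.** The point holds as a mismatch between the conclusion the Discussion offers and the sample this study will have. At the stated alpha, the margin can be excluded only by a chance pattern with fewer events on half dose, and the probability is about 16% at the planning rates. Under the more lenient alpha it is about 28%, before any loss. The non-inferiority conclusion is improbable, and few events in both arms would not establish it.

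This rests on an absolute risk-difference margin, the planned 5% and 7%, and complete follow-up of 25 per arm. The 0 vs 0 result depends on alpha and method, but the low chance of success does not: it stays below 30% at the planning rates under either alpha. Severity: should be fixed.

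**What to change.** In the Discussion, replace the non-inferiority conclusion and the sentence on its value for dose choice with a statement of three things:
1. The 50-patient pilot makes no non-inferiority claim.
2. The 10% margin applies only to the full-size stage.
3. The pilot will report the difference in 12-month primary-endpoint risk with its 95% confidence interval, by a named score or exact method that remains valid when an arm has no events.

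The cost is a more modest claim and one added summary in the report. Nothing changes for patients or procedures.

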## Data availability statement

The datasets during analyzed and/or during the current study are available from the corresponding author upon reasonable request.

## Ethics statement

The studies involving human participants were reviewed and approved by Medical Ethics Committee Office, [name]. The patients/participants provided their written informed consent to participate in this study.

